### Outcomes

The primary outcome is health related quality of life using the St Georges Respiratory Questionnaire (SGRQ) [49] which has previously been shown to be responsive in a population with less advanced COPD [50]. The primary endpoint is 12 months from randomisation.

Secondary outcomes: self-reported health behaviours [smoking and physical activity (IPAQ)] [51], self-management activities, psychological morbidity (Hospital Anxiety and Depression Scale) [52], self-efficacy for managing their COPD and undertaking physical activity, MRC dyspnoea scale [53], health care utilisation (primary care consultations for COPD; prescriptions for antibiotics for COPD; hospital admissions for COPD; attendance at smoking cessation service), EuroQoL EQ-5D-5 L [54], physical activity at 1 year measured by accelerometry. Table 2 summarises the outcome measures and timing of assessment.

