### Statistical justification for sample size

The sample size has been determined to detect a significant difference in the SGRQ at 1 year. To have 80% power to detect a difference of 4 points (which is the minimal clinically significant difference [26] from a baseline total value of 39 [50], with a standard deviation of 15) at the 5% level of significance, 445 evaluable participants are required. We aim to recruit 556 participants, which allows for a 20% loss to follow-up.

This sample size is more than sufficient to detect an increase in physical activity in the intervention group. Assuming the intervention arm reaches 89 minutes of moderate intensity physical activity/week, and the control arm 55 minutes (SD = 70 mins), for 90% power at a 5% significance level, a sample size of 90 patients in each arm is required (in absence of good COPD data, EXERT trial data used) [55]. Accounting for 20% loss-to follow-up, we therefore require a total of 225 patients. To estimate the power for smoking cessation we have taken a smoking prevalence of 45% [56]. Estimates of the likely quit rate are 34% in the intervention arm and 9% in the usual care arm (estimates from Cochrane review of nurse-led interventions for smoking cessation [53]). Our proposed sample size of 278 per group is sufficient to achieve power of 75%, at the 5% significance level.

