### Analysis

All data will be analysed by intention to treat. A comparison between groups for the primary outcome measures (health related quality of life) will be made at 1 year to assess the long-term effect of the self-management intervention.

For outcomes measured on a continuous scale (HRQoL, physical activity, EuroQol EQ-5D), analysis of covariance will be used; i.e. a linear regression where the final score is regressed against treatment group and adjusted for baseline score. Model assumptions will be checked and a transformation for Normality used if necessary. Binary outcomes will be analysed using logistic regression and recurrent outcomes (e.g. number of hospital admissions) will be analysed using Poisson regression with an offset term for the length of follow-up. Differences between treatment groups will be summarised with suitable effect estimates (e.g. mean difference, relative rate) with 95% confidence intervals. A 5% statistical significance level will be used. Levels and patterns of missing data will be assessed and summarised, and if appropriate, suitable methods (e.g. regression imputation using baseline data) will be used to evaluate any effect this might have on the conclusions.

We will undertake exploratory subgroup analyses to explore the effects of the intervention in a subgroup who actively engage with the intervention (through increased physical activity, uptake of smoking cessation support or checking of inhaler technique) and those who increase their self-efficacy for COPD self-management. Additionally we will explore effectiveness in subgroups by baseline level of self-efficacy, depression and anxiety scores and HRQoL and participant characteristics (age, sex, ethnicity and number of co-morbidities).

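### Poisson regression is specified for recurrent outcomes with no stated allowance for overdispersion; if counts vary more than Poisson, intervals will be too narrow and type I error above 5%

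*Protocol article*

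**What the plan says.** In the protocol article, the Analysis section assigns a model to each type of outcome. For counts it says that "recurrent outcomes (e.g. number of hospital admissions) will be analysed using Poisson regression with an offset term for the length of follow-up". Results are to be given as "suitable effect estimates (e.g. mean difference, relative rate) with 95% confidence intervals", and "A 5% statistical significance level will be used".

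The section has one sentence on checking assumptions: "Model assumptions will be checked and a transformation for Normality used if necessary". It comes directly after the description of the analysis of covariance and before the sentence on logistic and Poisson regression.

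The Outcomes section lists, among the secondary outcomes, "health care utilisation (primary care consultations for COPD; prescriptions for antibiotics for COPD; hospital admissions for COPD; attendance at smoking cessation service". Hospital admissions are the only one of these that the Analysis section names as a recurrent outcome. The article gives no expected event rate, variance or dispersion for any of them.

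**The concern.** A Poisson model takes the variance of a count to equal its mean, given the covariates and follow-up time. When people differ in their underlying rates, the variance exceeds the mean and the model-based standard error of the log rate ratio is too small.

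The article itself gives reason to expect such differences. The Intervention section singles out participants with repeated exacerbations who already hold an action plan and rescue medication. The section on the need for a trial notes that mild symptoms can coexist with more than mild airflow obstruction. The Poisson sentence names an offset but no covariate that might absorb these differences. The one remedy stated for a failed assumption, a transformation to Normality, belongs to the linear model and does nothing for excess variation in counts.

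At stake is a secondary claim that readers would act on: that coaching reduces admissions or other health care use. If the standard error is understated, chance differences will be declared significant too often.

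**Working it through.** **The plan's own figure.** There is none to reproduce. The article states no power, rate or dispersion for a count outcome.

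**Inputs from the article.** Significance level 5% (two-sided assumed, as the article does not say). Sample size: "445 evaluable participants are required", so about 445/2 ≈ 222 per arm. Follow-up is 12 months.

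**Inputs assumed.** The variance/mean ratio φ; or, in the simulation, the mean rate per year and the negative binomial dispersion k, where variance = mean + k × mean², so φ = 1 + k × mean.

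**Step 1: approximation.** If variance = φ × mean, the Poisson standard error is too small by a factor √φ. Then

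- true type I error = 2 × [1 − Φ(1.96/√φ)]
- Poisson interval width (log scale) = 1/√φ of the correct width

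| φ (assumed) | 1.96/√φ | Type I error | Width relative to correct |
|---|---|---|---|
| 1 | 1.960 | 5.0% | 100% |
| 1.2 | 1.789 | 7.4% | 91% |
| 1.5 | 1.600 | 11.0% | 82% |
| 2 | 1.386 | 16.6% | 71% |
| 3 | 1.132 | 25.8% | 58% |

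At φ = 2 the correct interval is √2 = 1.41 times the Poisson one, or 41% wider.

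**Step 2: simulation.** Negative binomial counts with no treatment effect, 222 per arm, equal one-year follow-up, 8,000 replicates per setting. Each entry is the rejection rate of the Poisson Wald test on the log rate ratio. The Monte Carlo standard error at 5% is √(0.05 × 0.95/8000) ≈ 0.24 percentage points.

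| Mean per year | k = 0 | k = 0.5 | k = 1 | k = 2 |
|---|---|---|---|---|
| 0.05 | 4.1% | 4.9% | 4.5% | 5.0% |
| 0.1 | 5.2% | 5.0% | 5.7% | 7.2% |
| 0.5 | 5.3% | 7.7% | 11.0% | 15.5% |
| 1.0 | 4.9% | 10.5% | 16.5% | 25.4% |
| 2.0 | 5.3% | 16.1% | 25.1% | 38.8% |

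The two steps agree where φ matches: mean 1 with k = 1 gives φ = 2 and 16.5%, against 16.6% from the formula.

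**Step 3: the same data with a standard error based on the observed variance.** Over the settings with k > 0, rejection rates are 3.9% to 5.4% at means of 0.05 to 0.1. Over all settings at means of 0.5 to 2 they are 4.7% to 5.6%. The remedy restores the nominal level where it had been lost, and is slightly conservative at the lowest rate.

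**Step 4: why rarity matters.** Since φ = 1 + k × mean, reaching φ = 2 at a mean of 0.1 needs k = (2 − 1)/0.1 = 10, and φ = 3 needs k = 20. These are extreme degrees of heterogeneity. For rare events the larger figures in Step 1 should therefore not be expected.

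**The case against.** The strongest objection is that this is a condensed article and the analysis plan is not shown. The sentence names a model family and an offset. It does not name a variance estimator, and it excludes neither a dispersion check nor a fallback. Poisson regression with robust standard errors would satisfy it as written. This stands in part: nobody can say that the trial will use the unadjusted standard errors. But the article does not leave the model open. It specifies Poisson regression, and a literal reading gives model-based intervals. An analysis plan that followed it word for word would carry the weakness forward.

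Four stronger readings are tempting, and the documents do not support them.

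- *That the intervals will be too narrow.* This depends on overdispersion, which is likely but not quantified anywhere in the article.
- *That Poisson regression is fixed for admissions, consultations and prescriptions alike.* Only admissions are named, as an example. Extending it to the other two is a reasonable inference, but they could also be analysed as any versus none by logistic regression.
- *That inflation of 11% to 26% applies to admissions.* Entry is restricted to MRC grades 1 and 2, and the Background attributes inpatient costs largely to severe disease, so low admission rates are plausible. At assumed means of 0.05 to 0.1 per year, type I error is about 4.5% to 5.7% for k of 0.5 to 1 and reaches 7.2% only at mean 0.1 with k = 2.
- *That the economic evaluation is distorted.* The within-trial analysis costs resource use directly and expresses uncertainty through sensitivity analysis and acceptability curves. It does not use the Poisson standard error. Nor does overdispersion bias the rate ratio itself when the model for the mean is right.

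**Conclusion.** The point holds in conditional form. The article specifies Poisson regression for recurrent outcomes and states no provision for overdispersion. If participants' event rates differ, as is likely, model-based intervals will be too narrow and the 5% test will be anti-conservative.

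The size depends on assumptions about rate and dispersion that the article does not supply. It ranges from negligible for rare admissions with moderate dispersion to serious for commoner events: 7.7% to 38.8% at assumed means of 0.5 to 2 per year with k from 0.5 to 2. The direction is not in doubt; the amount is.

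Only secondary outcomes are touched. The SGRQ comparison and the sample size built on it do not depend on this model. The change is still worth making, because a valid alternative is available at almost no cost.

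**What to change.** Amend the sentence on recurrent outcomes so that it names a method valid under overdispersion. For example: recurrent outcomes will be analysed by negative binomial regression with log follow-up time as offset, or by Poisson regression with robust standard errors if that model does not converge; results will be reported as rate ratios with 95% confidence intervals. The order of the two methods should be set before the data are seen. If an analysis plan already provides for this, it is enough to confirm it there.

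It would also help to state which health care utilisation outcomes are analysed as counts.

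The cost is one sentence and somewhat wider intervals where counts are overdispersed; where they are not, little is lost. Adjusting these models for centre or for the baseline count is a separate matter and is not needed to resolve this point.

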### Follow up assessments

Outcomes are measured at six months to determine short–term changes to the end of the intervention and 1 year to determine whether change is sustained.

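### Regression imputation from baseline data, the only missing-data method named, is a weak check on the primary ANCOVA under 20% loss and leaves out the 6-month SGRQ

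*Protocol article*

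**What the plan says.** The Analysis section of the protocol article makes the primary comparison an ANCOVA of 12-month SGRQ: "a linear regression where the final score is regressed against treatment group and adjusted for baseline score". On missing data it begins "Levels and patterns of missing data will be assessed and summarised, and if appropriate" and continues "suitable methods (e.g. regression imputation using baseline data) will be used to evaluate any effect this might have on the conclusions". No other method is mentioned. The text does not say whether the imputation is single or multiple, whether random error is added to the predicted values, whether arm is in the model, or which baseline variables are used.

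The sample size section plans for substantial loss: "We aim to recruit 556 participants, which allows for a 20% loss to follow-up". The Follow up assessments section says "Outcomes are measured at six months" as well as at one year, and Table 2 lists SGRQ at baseline, 6 months and 12 months.

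**The concern.** A sensitivity analysis for missing data is useful if it brings in information that the main analysis lacks, or relaxes one of its assumptions. The primary ANCOVA already conditions on arm and baseline SGRQ. Filling in missing 12-month scores from those same two variables adds nothing, and analysing the filled-in values as if observed overstates precision.

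The most relevant additional variable is SGRQ at 6 months, which comes after the telephone contacts and written prompts have ended. The Data monitoring committee section describes the trial as unblinded, and the outcome is self-reported. It is therefore plausible that people leave after 6 months partly according to how they have fared, and differently in the two arms. A check built only on baseline data sees little of that. An analyst who follows the protocol's one example could report that the conclusions are robust when the check had little power to show otherwise.

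**Working it through.** **Inputs from the sample size section.** "To have 80% power to detect a difference of 4 points", "with a standard deviation of 15", "at the 5% level of significance, 445 evaluable participants are required"; 556 recruited, 278 per group, 20% loss. A two-sided test is assumed.

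**The plan's own figure.** n per arm = 2 × (1.960 + 0.842)² × 15² / 4² = 220.8, so 221 per arm and 442 in total. The t-test version gives 222 per arm and 444 in total. Power at 445 is 80.3%. Inflation gives 445 / 0.8 = 556.25. The stated 445 and 556 reproduce.

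**Single deterministic imputation, arm and baseline SGRQ in the model.** Each imputed value lies on the plane fitted to the 445 observed cases, so its residual is zero. Refitting to all 556 gives the same coefficients and the same residual sum of squares. Two things change:
- the residual degrees of freedom rise from 445 − 3 = 442 to 556 − 3 = 553;
- the apparent information rises by about 556/445.

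The SE factor is therefore sqrt((445/556) × (442/553)) = sqrt(0.8004 × 0.7993) = 0.80. A nominal 5% test uses an effective critical value of 1.96 × 0.80 = 1.568, which gives a two-sided error rate of about 11.7% and coverage of about 88.3%. Only the 20% loss, taken as equal in the two arms, enters this calculation. No correlation is needed.

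**The same, with arm left out.** Imputed values carry no arm difference, so the effect shrinks by the missing fraction: 4 × (1 − 0.20) = 3.2.

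**Simulation.** There were 800 runs with N = 556, about 20% missing, a true effect of −4 and 20 imputations. The following are assumptions, not document figures:
- total SD 15 and baseline coefficient 0.7;
- one further prognostic baseline covariate (−3 points per SD);
- a 6-month score with residual SD 8, of which 0.6 carries through to 12 months;
- the 6-month score observed for everyone.

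| Dropout | Method | Mean estimate | Mean SE | Coverage |
|---|---|---|---|---|
| Completely at random | Complete-case ANCOVA | −4.03 | 1.017 | 95% |
| | Single deterministic, arm + baseline SGRQ | −4.03 | 0.813 | 88% |
| | Single deterministic, no arm | −3.22 | 0.816 | 84% |
| | Single stochastic, arm + baseline SGRQ | −4.03 | 0.909 | 90% |
| | Multiple imputation, arm + baseline SGRQ | −4.03 | 1.023 | 95% |
| Depends on the other baseline covariate, opposite directions by arm | Complete-case ANCOVA | −2.92 | 1.017 | 81% |
| | Multiple imputation adding that covariate | −4.00 | 1.036 | 95% |
| Depends on 6-month SGRQ, opposite directions by arm | Complete-case ANCOVA | −5.09 | 1.007 | 80% |
| | Multiple imputation, arm + all baseline variables | −4.88 | 1.006 | 86% |
| | The same plus 6-month SGRQ | −3.99 | 0.993 | 96% |

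In the last scenario the complete-case bias is 5.09 − 4 = 1.09 points. Baseline-only multiple imputation leaves 4.88 − 4 = 0.88, which is 0.88/1.09 = 81% of it. Adding the 6-month score removes it.

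**The case against.** The strongest reply is that the protocol does not commit to any of this. The method is introduced as an example and made conditional on what the missing data look like. The wording leaves room for any suitable method, including the one proposed here. Regression is the usual engine of multiple imputation, and the full imputation model normally belongs in a SAP, which is not shown.

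Much of that stands. A reader might infer that the planned check must either reproduce the complete-case result with too small an SE or dilute the effect, and so can never reveal selective dropout. The documents do not support that:
- The text does not say single imputation. Stochastic imputation gives an SE about 11% below the complete-case SE rather than 20%, and multiple imputation gives a sound one.
- Baseline data are wider than baseline SGRQ. The Baseline assessments section and Table 2 include all the outcome measures, demographics, spirometry, medications and comorbidities. In the second dropout scenario, using such a variable moved the estimate from −2.92 to −4.00.

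The objection does not dispose of the choice of predictors. The protocol is not silent here: it names one method and limits it to baseline data. That limit omits the 6-month SGRQ whether imputation is single or multiple. It is also fair to say that the 6-month score helps only for people who returned it, a share the documents do not give, and that the dropout mechanism simulated was a strong one.

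**Conclusion.** The point holds in a limited form. As an example, regression imputation from baseline data is poorly matched to an ANCOVA already adjusted for baseline and to a visit schedule with a 6-month SGRQ.

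Two figures are firm but conditional. They apply to single deterministic imputation with 20% missing equally in both arms: an SE about 20% too small if the model holds arm and baseline SGRQ, or about 20% dilution of the effect if it holds baseline SGRQ without arm. The inflated error rate would matter only if that analysis were used for inference.

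The 6-month point does not depend on how the imputation is done. Its size (about 80% of the bias left in the scenario run) does rest on assumed correlations, complete 6-month data and dropout running in opposite directions by arm.

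The weakness concerns a sensitivity analysis. It is worth correcting, but it does not undermine the primary analysis or the sample size.

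**What to change.** Keep the 12-month ANCOVA as the primary analysis. Replace the example with multiple imputation that includes arm (or is run separately by arm), 6-month SGRQ, baseline covariates and centre. A mixed model of 6- and 12-month SGRQ would serve as an alternative sensitivity analysis, but should not displace the ANCOVA.

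Both of these assume data are missing at random, so add a delta-adjusted analysis for dropout that depends on the unseen score. The trial team should choose the range in advance, since the documents give no basis for one. As a guide, with 20% missing in the intervention arm, shifting the imputed scores in that arm by d points moves the estimate by about 0.20 × d, so a 5-point shift moves it by about 1 point.

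The cost is a change of wording and some extra programming and analysis time. No new data are needed.

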### Intervention fidelity

A sample of telephone consultations are being recorded with the participants consent. These will be assessed according to delivery of the planned components, the use of behavioural change techniques and patient centred approach. The nurses delivering the intervention record the number of contacts and actions taken; these records will be used to assess the proportion of the intervention participants who participated in the intervention, the number of calls per participant and the number who completed all six intervention contacts.

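### Two exploratory analyses are described as subgroup effects of the intervention, but their groups are defined by what happens after randomisation, so they do not estimate such an effect

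*Protocol article*

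**What the plan says.** The Analysis section puts intention to treat first and fixes the primary comparison at 1 year, using linear regression adjusted for the baseline score. It then announces exploratory subgroup analyses. The first is "to explore the effects of the intervention in a subgroup who actively engage with the intervention (through increased physical activity" or by either of two other routes, taking up help to stop smoking and having inhaler technique checked). The second group consists of "those who increase their self-efficacy for COPD self-management". A separate sentence adds subgroups by baseline self-efficacy, depression and anxiety, HRQoL and participant characteristics.

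The Outcomes section lists several of the variables that define the first two groups as secondary outcomes: self-reported and accelerometer-measured physical activity, attendance at a smoking cessation service, and "self-efficacy for managing their COPD and undertaking physical activity". Inhaler checks are not listed there by name.

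Under Intervention fidelity, the nurses' records will give "the number of calls per participant and the number who completed all six intervention contacts". By Table 1 those six contacts are four telephone calls (weeks 1, 3, 7 and 11) and two postal ones (weeks 16 and 24).

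**The concern.** A subgroup effect is interpretable when membership is fixed before randomisation, because the two arms within the subgroup are then comparable. Here membership depends on later behaviour or on a later score.

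There are two natural ways to run the analysis, and neither gives an intervention effect:

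- **Engagers in the coaching arm against all controls.** This sets a self-selected group beside an unselected one. People who take up activity or attend services may well have had a better 12-month SGRQ without coaching.
- **Improvers in both arms.** This conditions on something coaching is meant to change, so improvers in the two arms are different kinds of people.

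Timing adds a further problem. Table 2 places accelerometry only at baseline and 12 months. A group defined by it is identified at the same follow-up as the primary outcome, and feeling better may be the reason for moving more.

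What is at stake is interpretation. If the intention-to-treat result were null, a finding that coaching works in those who engage could be selection alone, yet the protocol's wording would allow it to be reported as an effect.

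**Working it through.** **1. The plan's own figure.** Inputs from the sample-size section: "To have 80% power to detect a difference of 4 points", "with a standard deviation of 15", and "at the 5% level of significance, 445 evaluable participants are required". Two-sided testing is assumed.

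n per arm = 2(1.96 + 0.842)² × 15² / 4² = 220.7, so 221 per arm and 442 in total. The t-test version gives 222 per arm, 444 in total. The stated 445 agrees, and 445 / 0.8 = 556.25 matches the 556 to be recruited. The SD of 15 and the 4-point target can therefore be carried forward.

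**2. Engagers against all controls, true effect zero.** Let q be the share of the coaching arm classed as engaged, and r the correlation between a normally distributed engagement tendency and a better 12-month SGRQ. The protocol gives neither, so both are assumptions. The expected spurious benefit is

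b = r × SD × λ(q), with λ(q) = φ(c)/q and c the normal point exceeded with probability q.

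λ(0.3) = 0.3477/0.3 = 1.159; λ(0.5) = 0.3989/0.5 = 0.798; λ(0.7) = 0.3477/0.7 = 0.497.

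For the planned ANCOVA, SD is replaced by 15√(1 − ρ²), where ρ is the baseline to 12-month correlation (assumed 0.5 to 0.7). This gives 12.99 to 10.71. Here r is the correlation with the part of the 12-month score that baseline does not explain.

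| Setting | r = 0.1 | r = 0.2 | r = 0.3 |
|---|---|---|---|
| q = 30%, unadjusted | 1.74 | 3.48 | 5.22 |
| q = 50%, unadjusted | 1.20 | 2.39 | 3.59 |
| q = 70%, unadjusted | 0.75 | 1.49 | 2.24 |
| q = 30%, ρ = 0.5 | 1.51 | 3.01 | 4.52 |
| q = 50%, ρ = 0.5 | 1.04 | 2.07 | 3.11 |
| q = 30%, ρ = 0.7 | 1.24 | 2.48 | 3.72 |
| q = 50%, ρ = 0.7 | 0.85 | 1.71 | 2.56 |

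The correlation needed for a spurious 4 points is 4/(SD × λ):

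- Unadjusted: 0.23, 0.33 and 0.54 at q = 30%, 50% and 70%.
- After ANCOVA: 0.27-0.32, 0.39-0.47 and 0.62-0.75.

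**3. False-positive rate at q = 50%.** With 222.5 evaluable per arm, SE = 15√(1/111.25 + 1/222.5) = 1.74. The chance of p < 0.05 is Φ(b/SE − 1.96) + Φ(−b/SE − 1.96), which is 11%, 28% and 54% for r = 0.1, 0.2 and 0.3, against a nominal 5%.

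A simulation of the ANCOVA (222 per arm, 1,500 runs per setting) agrees. At r = 0.3 the mean spurious difference is −3.58 with 55% rejection (ρ = 0), and −2.85 with 54% rejection (ρ = 0.6). With no selection (r = 0) the bias is about zero and rejection is 4-6%. Baseline adjustment shrinks the bias in points but leaves the false-positive rate about where it was.

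**4. One definition applied in both arms.** The spurious benefit is r × SD × [λ(q coaching) − λ(q control)].

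- 50% of the coaching arm and 30% of controls, r = 0.3: 0.3 × 15 × (0.798 − 1.159) = −1.62, that is, 1.6 points against the intervention (1.4 after ANCOVA with ρ = 0.5).
- 60% and 20%, r = 0.3, unadjusted: −3.4.
- Equal shares and the same selection process in both arms: zero.

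**The case against.** The analyses are labelled exploratory and come after a clear intention-to-treat primary analysis. No decision in the protocol depends on them: the longer-term economic model is conditional on effectiveness within the trial, with no mention of engagers. The comparator is not stated, and an analysis plan could properly fix it. A common definition in both arms is at least partly feasible, since Table 2 collects IPAQ, self-management activities and self-efficacy without restriction by arm, and every participant is asked about smoking cessation attendance at six months.

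Most of this stands. It removes any threat to the primary result, and it means the direction of bias cannot be stated in advance. It does not rescue the wording. The protocol itself names intervention effects in these groups as the target, so this is not detail left to another document. An exploratory label warns of chance findings and multiplicity, not of systematic bias.

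A reader might infer that a null trial would very probably show a 4-point benefit in engagers. The documents do not support that. They give neither q nor r. Over correlations of 0.1-0.3 and shares of 30% and 50%, only one of the six unadjusted values exceeds 4 points, and with ρ = 0.7 none does. Nor does the protocol merge these groups with the baseline-defined ones, which have their own sentence and do not share the fault.

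**Conclusion.** The point holds as a fault in what the two analyses claim to estimate. Groups formed by engagement or by rising self-efficacy arise after randomisation, and a contrast within them is not an intervention effect.

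For engagers against all controls, with no true effect, SD 15, r of 0.1-0.3 and 30-50% engaged, the artefact is about 1.2 to 5.2 points unadjusted. It is about 0.9 to 4.5 points after ANCOVA with ρ of 0.5-0.7. The trial's target is 4 points. With 70% engaged it is 2.2 points or less over the same correlations. With one definition in both arms it may be near zero or go against coaching. All of these shares and correlations are assumptions.

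It would be tempting to treat this as a flaw in the trial's main conclusion. It is not: the primary comparison and the sample size are untouched. The correction concerns secondary interpretation and should be made before these analyses are run.

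**What to change.** Stop describing these two analyses as effects of the intervention in subgroups. Then do one of the following.

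1. **Report them as descriptive associations only.** This is enough to cure the fault.
2. **Replace them with analyses whose assumptions are stated:**
   - *Engagement:* a complier-average causal effect with randomisation as instrument and the recorded contacts as adherence. The threshold must make the exclusion restriction plausible. Requiring all four calls would strain it, because people with fewer calls still receive coaching and materials. Receipt of any coaching call, or a dose-response version using the number of contacts, is easier to defend. This addresses receipt of coaching, not the behavioural engagement the protocol describes.
   - *Self-efficacy and activity:* a mediation analysis with 6-month self-efficacy and 6-month IPAQ as mediators and 12-month SGRQ as outcome, adjusted for baseline values, with a sensitivity analysis for unmeasured confounding.

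In either case, keep the baseline-defined subgroups, test them by interaction, and reserve the term subgroup effect for them.

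**Cost:** changes of wording, some extra analysis and no new data. Under option 2 the intervals are wider and the analyses rest on explicit assumptions that cannot be tested. The 6-month activity mediator is self-report only, because accelerometry is taken at baseline and 12 months.
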